|                                      | 
procedure as was used at baseline
 
All patients will receive clopidogrel at 75 mg daily for a period of at least 6 months. Ticlopidine at a dose standard with hospital practice may be substituted for clopidogrel, as required by hospital practice or if the patient develops hypersensitivity to clopidogrel.
 
All patients will receive <math>\geq 75</math> mg of aspirin daily for a minimum of five years following the procedure
                                                                                                                                                                                                                                                                                                                                                                                                                       |
| Key Inclusion Criteria        | 
 
• Females, at least 18 years of age and able to provide informed consent
 
• Patient must have evidence of myocardial ischemia
 
• Patient must be an acceptable candidate for coronary artery bypass graft (CABG) surgery
 
• Patient must agree to undergo all CIP-required follow-up examinations
 
• Patients' artery morphology and disease is suitable to be optimally treated with a maximum of 4 planned study stents
 
• Target lesions must be de novo lesions (no prior stent implant, no prior brachytherapy)
 
• Target vessel reference diameter must be between 2.5 mm and 4.0 mm by visual estimate. The diameter range will be expanded to 2.25 mm when the 2.25 mm stent is available.
 
• Target lesion <math>\leq 28</math> mm in length by visual estimate
 
 |
| Key Exclusion Criteria        | 
 
• Participation in another device or drug study or has completed the follow-up phase of another study within the last 30 days
 
• Patient has had a previous stent implant, either BMS or DES within the target vessel(s)
 
                                                                                                                                                                                                                                                                                                                                                                                                                                                                                                                                                                                                 |
| Primary Analytical Population | 
Intent to treat population for all endpoints.
                                                                                                                                                                                                                                                                                                                                                                                                                                                                                                                                                                                                                                                                                                                                                                                                                               |

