| Secondary Endpoints | 
Acute Success (Clinical Device Success and Clinical Procedure Success)
 
Adjudicated Stent Thrombosis at 30 days, 240 days and at 1, 2, 3, 4 and 5 years (Definite, Probable, Possible)
 
Adjudicated revascularization (TLR/TVR/all revascularizations) at 30 days, 240 days and at 1, 2, 3, 4 and 5 years
 
Adjudicated Composite rate of Cardiac Death, MI attributed to the target vessel and CI-TLR at 30 days, 240 days and at 1, 2, 3, 4 and 5 years.
 
Adjudicated Composite rate of all Death, all MI and Target Vessel Revascularization (TVR) at 30 days, 240 days and at 2, 3, 4 and 5 years.
 
Adjudicated Composite rate of all Death, all MI and all Revascularization (TLR/TVR/non TVR) at 30 days, 240 days and at 1, 2, 3, 4 and 5 years.
 
Adjudicated Cardiac Death, Non-Cardiovascular Death, Vascular Death, Q-wave MI and Non Q-wave MI (Peri-Procedural, Unrelated to PCI) at 30 days, 240 days and at 1, 2, 3, 4 and 5 years.
 
In-stent Late Loss (LL) at 270 days (main secondary endpoint for the randomized sub-study)
 
In-segment Late Loss (LL) at 270 days (for the randomized sub-study)
 
In-stent and in-segment Angiographic Binary Restenosis rates at 270 days (for the randomized sub-study)
 
In-stent and in-segment percent Diameter Stenosis at 270 days (for the randomized sub-study)
 
Aneurysm, thrombus and persisting dissection at 270 days (for the randomized sub-study)
 |

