#### **7.3.2 Baseline Angiography**

The angiogram acquired during the index procedure (i.e. the baseline angiography) will be assessed visually and parameters will be documented in the eCRF.

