### **Clinical Device Success**

Successful delivery and deployment of the study stent (in overlapping stent setting a successful delivery

and deployment of the first and second study stent) at the intended target lesion and successful withdrawal of the stent delivery system with attainment of final residual stenosis of less than 50% of the target lesion by visual estimation, without use of a device outside the assigned treatment strategy. Standard pre-dilation catheters and post-dilatation catheters (if applicable) may be used. Bailout patients will be included as clinical device success only if the above criteria for clinical device success are met.

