#### **Clinical Procedure Success**

Successful delivery and deployment of the study stent or stents at the intended target lesion and successful withdrawal of the stent delivery system with attainment of final residual stenosis of less than 50% by visual estimation, using any adjunctive device without the occurrence of cardiac death, MI attributed to the target vessel and/or CI-TLR during the hospital stay with a maximum of first seven days post index procedure. In multiple lesions setting each lesion must meet clinical procedure success.

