#### **Late Loss (LL)**

General definition: Calculated as MLD post-procedure – MLD at follow-up

- **In-segment Late Loss:** in-segment MLD post-procedure – in segment MLD at follow-up
- **In-stent Late Loss:** in-stent MLD post-procedure – in-stent MLD at follow-up
- **Proximal Late Loss:** proximal MLD post-procedure – proximal MLD at follow-up (proximal defined as within 5 mm proximal to stent placement)
- **Distal Late Loss:** distal MLD post-procedure – distal MLD at follow-up (distal defined as within 5 mm distal to stent placement)

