#### **Minimum Lumen Diameter (MLD)**

The average of two orthogonal views (when possible) of the narrowest point within the area of assessment – in lesion, in stent or in segment. MLD is visually estimated during angiography by the Investigator; it is measured during QCA by the Angiographic Core Lab.

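### Minor: in the randomised sub-study, the residual-stenosis part of Acute Success should use core-laboratory QCA of the final film, not the operator's visual estimate

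*Protocol*

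**What the plan says.** The Clinical Investigation Plan Summary and Section 5.2 name "Acute Success (Clinical Device Success and Clinical Procedure Success") as a secondary endpoint. The clinical event endpoints listed after it are adjudicated; this one is not described so.

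Appendix II fixes the stenosis criterion. Clinical Device Success needs "attainment of final residual stenosis of less than 50% of the target lesion by visual estimation". Clinical Procedure Success needs "attainment of final residual stenosis of less than 50% by visual estimation". Neither definition separates the Single Arm Study from the randomised sub-study.

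On who reads the film, Section 7.3.2 says that the index-procedure angiogram "will be assessed visually and parameters will be documented in the eCRF". The Appendix II entry for minimum lumen diameter states: "MLD is visually estimated during angiography by the Investigator; it is measured during QCA by the Angiographic Core Lab".

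On what else is measured, Section 7.3.5 has the sub-study's post-stent angiography follow the core laboratory's guidelines. In-stent late loss, the main secondary endpoint of the sub-study, starts from "in-stent MLD post-procedure". Appendix II defines percent diameter stenosis as a QCA quantity, 100 × (1 − MLD/RVD).

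**The concern.** Section 9.3.1 analyses sub-study patients by randomised arm and Section 9.4 applies this to the sub-study endpoints, so Acute Success will be shown for XIENCE against CYPHER. Part of that figure depends on how the person who did the procedure, and who knows which stent was used, judges the result. A separate reader's measurement of the same film should exist for most of these lesions.

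If operators graded one stent more leniently near the 50% threshold, the difference would appear as a treatment effect. If they were equally lenient with both stents, there would be no false difference, but success would be overstated in both arms.

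**Working it through.** **The plan's own figures.** The protocol gives no rate, difference or power for Acute Success, so there is nothing to reproduce for this endpoint. The only sub-study calculation (Section 9.2) concerns late loss: one-sided α 0.05, power 90%, SD 0.53 mm, margin 0.17 mm, 2:1 allocation, true difference 0. The normal approximation gives n(CYPHER) = (1.645 + 1.282)² × 0.53² × 1.5 / 0.17² = 124.9, that is 125 and 250. The noncentral t gives 126 and 252 with power 90.1%, which are the plan's numbers. That calculation is sound and unaffected.

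**The texts side by side.**

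1. *Criterion.* Both components use a visual reading below 50% (Appendix II), in both parts of the study.
2. *Reader.* The success definitions do not name the reader. Section 7.3.2 and the MLD and RVD entries in Appendix II point to the investigator.
3. *Knowledge of arm.* The sub-study is single-blind (Section 9.1), without saying who is blinded. The operator must implant the allocated stent (Section 7.3.3.2), so the operator knows the arm.
4. *Alternative reading.* No single sentence says that the core laboratory measures every post-stent film. It follows from Section 7.3.5 together with the late loss and MLD definitions: without a QCA post-procedure MLD there is no late loss.
5. *The plan's standard elsewhere.* At follow-up the same 50% threshold is read by QCA for binary restenosis (Appendix II). For target lesion revascularisation the core laboratory checks stenosis severity and can overrule the investigator (Appendix II). For sub-study revascularisations it supplies QCA diameter stenosis to the events committee (Section 8.6.1).

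**Scale only.** With about 150 CYPHER and 300 XIENCE patients (Section 9.2), one patient is 1/150 = 0.67 points or 1/300 = 0.33 points. That is the step size of any binary endpoint at these arm sizes, not an estimate of bias.

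**Illustration on assumed values.** Let a share q of patients in each arm fail the criterion by QCA, and let the visual reading miss a share m of those failures. Visual success is 1 − q(1 − m), and the false difference is q × (m_XIENCE − m_CYPHER). All other components are taken as met.

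| q | missed, XIENCE / CYPHER | visual success, XIENCE / CYPHER | false difference |
|---|---|---|---|
| 2% | 50% / 50% | 99.0% / 99.0% | 0 |
| 2% | 75% / 25% | 99.5% / 98.5% | 1.0 point |
| 2% | 100% / 0% | 100% / 98.0% | 2.0 points |
| 5% | 50% / 50% | 97.5% / 97.5% | 0 |
| 5% | 75% / 25% | 98.75% / 96.25% | 2.5 points |
| 5% | 100% / 0% | 100% / 95.0% | 5.0 points |

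Exchanging the miss rates reverses the sign. In the equal-miss rows, success is overstated by 1.0 and 2.5 points in both arms. For comparison, exact 95% intervals at an assumed 98% success are 95.7% to 99.3% for 294/300 and 94.3% to 99.6% for 147/150.

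**The case against.** The strongest reply is that nothing here is contradictory. The endpoint is a clinical success measure, one definition serves about 2000 patients, and no core-laboratory QCA is described for the roughly 1550 in the Single Arm Study. The protocol asks for QCA where it wants it. Section 9.4 makes Acute Success descriptive and rests sub-study success on late loss. A QCA line could be added in an analysis plan that is not shown here.

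Most of this stands, and it sets the weight. The visual version is needed for the Single Arm Study and for pooling. The reply does not remove the point, because Appendix II itself fixes the weaker reading for the randomised comparison, where a better one should be to hand.

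Four stronger readings are tempting, and the documents do not support them:

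- *That the comparison is biased by a known amount.* No rate is given, the shares in the illustration are assumptions, and only lesions that the two readings place on opposite sides of 50%, unequally by arm, would matter. Their number may be zero.
- *That the core laboratory reads blind to stent.* This is not stated; it is only a separate reader.
- *That QCA exists for every lesion at no cost.* This is inferred. A stent that was never deployed has no in-stent measurement, and Section 9.6 drops missing data, so a QCA definition without a fallback could lose some of the clearest failures.
- *That QCA would make the endpoint objective.* Delivery, deployment and withdrawal remain operator-reported. The death, infarction and revascularisation part of procedure success already rests on event types that the events committee adjudicates.

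**Conclusion.** The point holds as a cheap improvement of minor weight. In the randomised sub-study, the residual-stenosis part of both Acute Success components is read by someone who knows the arm, while the main secondary endpoint already requires a core-laboratory measurement of the same film. Two inferences carry this: that the operator makes the visual reading and knows the arm, and that post-procedure QCA is done wherever late loss is to be calculated. Both are firm, though neither is stated in one sentence.

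No size of bias can be derived. A reader might infer that the sub-study's conclusion is at risk, or that being listed first gives Acute Success special rank. Neither follows: late loss is the only ranked secondary endpoint, and the primary endpoint, the non-inferiority test and the sample size do not depend on Acute Success.

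**What to change.** In Appendix II, for the between-arm comparison in the randomised sub-study:

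- define the residual-stenosis part of Clinical Device Success and Clinical Procedure Success as below 50% by core-laboratory QCA of the final angiogram;
- use the visual estimate only where QCA is not available, and report how often that happened in each arm;
- count patients whose study stent was not delivered or deployed as failures, so that none drop out under the available-data rule in Section 9.6.

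Keep the visual version for the Single Arm Study, for the pooled analysis and as a supporting line in the sub-study, so that the two parts can still be compared.

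The cost is one clause with its fallback rule and one more table row; no additional imaging should be needed. The small downside is two readings to report and explain.

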# 1 INTRODUCTION

The SPIRIT WOMEN Clinical Evaluation is a prospective, open label, single arm, multi-center study evaluating performance of the XIENCE Everolimus Eluting Coronary Stent System (XIENCE V EECSS) in the treatment of female patients with coronary artery lesions, per its Instructions for Use (IFU). Additionally, this study will include a prospective, single-blind, double arm, randomized multi-center sub-study comparing the XIENCE EECSS (XIENCE V EECSS and XIENCE PRIME EECSS) to the CYPHER SELECT™ Plus Sirolimus-eluting Coronary Stent in the treatment of female patients with coronary artery lesions.

- Approximately 1550 patients will be enrolled in the single arm study (SPIRIT WOMEN Single Arm Study / SAS).
- Approximately 450 patients will be randomized 2:1 (XIENCE EECSS vs. CYPHER SELECT™ Plus Sirolimus-eluting Coronary Stent) from up to 35 selected sites (randomized sub-study). In the event a subsequent generation of CYPHER SELECT™ Plus Sirolimus-eluting Coronary Stent is released during the course of the study, it may replace the CYPHER SELECT™ Plus Sirolimus-eluting Coronary Stent. (Randomized Sub-study / RSS)

The purpose of this clinical evaluation is to characterize the female population undergoing stent implantation and to continue the evaluation of the performance of XIENCE EECSS in this specific population in real-world use. Following initial stent implantation, all patients will have clinical follow-up at 30 days, 240 days and at 1, 2, 3, 4 and 5 years to assess the long term outcome of the stenting procedure. A sub group of patients (N = approximately 450) will have angiographic follow-up at 270 days (randomized sub-study).

## 2 BACKGROUND INFORMATION

### 2.1 Background and Rationale

#### 2.1.1 Literature Review

Coronary heart disease has been shown to be the leading cause of death in Western countries with approximately equal incidence in men and womeni. Due to increased life expectancy, particularly in women, the burden of the disease is increasing. General awareness is poor and women are likely to be diagnosed less often and at a later stage than menii,iii. As this is also demonstrated by a smaller representation of women in clinical studiesiii, one of the recommendations of the Policy Conference on Cardiovascular Diseases in Women of the European Society of Cardiology was to conduct clinical trials enrolling only female patientsi.

Stenting of *de novo* lesions in native coronary arteries has been shown to be a safe and effective treatment of occlusion due to atherosclerosisiv,v,vi,vii,viii,ix,x,xi,xii and use of drug-eluting stents is currently the standard procedure in the USA and Europe.

Studies evaluating the local application of anti-proliferative drugs (e.g., sirolimus, paclitaxel derivatives) for prevention of restenosis via a stent delivery system show that these therapies successfully inhibit or reduce restenosis and associated clinical eventsxiii,xiv,xv,xvi. The local application of anti-proliferative drugs may decrease the need for patients to undergo repeat percutaneous transluminal coronary angioplasty (PTCA) or coronary artery bypass graft (CABG). It may also aid in decreasing the high cost of medical care involved when these repeat interventions are required. Everolimus, a sirolimus analogue, is a drug found to be an effective anti-proliferative agent. It inhibits growth factor-stimulated cell proliferation by causing cell cycle arrest in the late G1 stage in the cell cyclexvii.

The feasibility of using everolimus on a drug eluting stent was demonstrated in the SPIRIT FIRST Study using the XIENCE V EECSS compared to the metallic, uncoated MULTI LINK VISION® RX Coronary Stent System (VISION® RX CSS) (N=60; N=28 for the everolimus cohort, and N=32 for the metallic stent cohort) in the treatment of patients with *de novo*, native coronary artery lesions. The primary endpoint, angiographic in-stent late loss, was observed at 0.10 mm for the XIENCE V EECSS, a reduction of 88% relative to the metallic control ( $p < 0.001$ ). This was matched by excellent proximal and distal late loss values of 0.10 mm and 0.07 mm, respectively, which indicated no edge effects. These observations were consistent with IVUS measurements, which showed the 180-day in-stent % Volume Obstruction in the XIENCE V EECSS arm to be 8.0 % while the control arm value was 28.1%. This represented a reduction of neointimal volume of 72% relative to the metallic stent control.

The SPIRIT FIRST study showed clinical safety of the everolimus-eluting stent delivered from a durable polymer coating at 30 days and 180 days: No stent thrombosis events, no instances of late acquired stent malapposition and a six-month hierarchical MACE (Major Adverse Cardiac Event) rate of 7.7%, compared to a MACE rate of 21.4% for the VISION® RX CSS arm.

The SPIRIT FIRST one year and two year results demonstrate a continuation of the treatment effect of the XIENCE V EECSS observed at 6 months, and a reduced rate of cell proliferation compared to the uncoated control. At 1 year, the superiority in efficacy, as measured by in-stent late loss, of XIENCE V as compared to VISION® RX was sustained (71% reduction in late loss). The XIENCE V arm also maintained at 1 year its superiority to the VISION® RX arm in the secondary IVUS endpoints, % volume obstruction and neointimal volume (64% and 65% reduction respectively). The overall MACE rate was 15.4% in the XIENCE V arm and 21.4% in the VISION® RX arm. No late stent thrombosis events were observed in either group up to the 1 year follow-up time point. Two years follow-up demonstrated that the treatment effect that was observed at 1-year was sustained: there were no observations of late thrombotic events, and no additional Target Vessel Failures between 1 year and 2 years in the XIENCE V arm.

The SPIRIT IIxviii Trial is a multi-center randomized controlled trial conducted in Europe to continue to assess the feasibility and performance of the XIENCE V EECSS in the treatment of subjects with a maximum of two *de novo* native coronary artery lesions each in a different epicardial vessel, compared to TAXUS® EXPRESS2 PECS. The trial enrolled 300 subjects at 28 sites; 223 subjects in the XIENCE V group, and 77 subjects in the TAXUS® group. Enrollment was completed in November, 2005. The SPIRIT II clinical trial includes clinical follow up at 30, 180, 270 days and 1- 5 years All patients were to have an angiographic follow-up at 180 days and a subset of 152 patients was to have an IVUS follow-up at 180 days and an angiographic and IVUS follow-up at 2 years.

The primary endpoint was met with an in-stent LL of  $0.11 \pm 0.27$  mm for the XIENCE V group compared to 0.36 mm for TAXUS® PECSS at 180 days, which represents a 72% reduction in late loss. As such, XIENCE V EECSS clearly demonstrated both non-inferiority ( $p < 0.0001$ ) and superiority ( $p < 0.0001$ ) to the TAXUS® PECSS in terms of the primary endpoint of in-stent late loss. The IVUS results support the angiographic endpoint results. There was a 66% reduction in %VO in the XIENCE V group as compared to the TAXUS® group (2.5% vs. 7.4%) and a 73% reduction in NIH volume (3.8 vs. 14.4 ) in XIENCE V group as compared to TAXUS® group. In addition, for other key clinical endpoints the XIENCE V group also tend to have lower observed event rates than the TAXUS® group, e.g. ID-TLR (1.8% vs. 3.9%), ID-TVR (2.7% vs. 5.2%), ID-MACE (2.7% vs. 6.5%). There was 0.5% Late Stent Thrombosis (1/223) in the XIENCE V group versus 1.3% (1/77) in the TAXUS® group. There were no additional MACE events or Stent Thrombosis between 180 days and 270 days follow-up. Therefore, the angiographic, IVUS results at 6 months, and clinical endpoint results through 9 months have demonstrated the safety and efficacy of the XIENCE V EECSS.

SPIRIT III, a pivotal clinical trial conducted in the USA and Japan, was designed to compare XIENCE V EECSS performance to the TAXUS PECSS. The SPIRIT III USA randomized clinical trial indicates that XIENCE V EECSS efficacy is statistically non-inferior to the TAXUS PECSS in single and multiple de novo native coronary artery lesions. Moreover, the primary endpoint was met with an in-segment late loss of  $0.14 \pm 0.41$  mm for the XIENCE V EECSS arm and  $0.28 \pm 0.48$  mm for the TAXUS PECSS arm at 240 days (non-inferiority  $p < 0.0001$ , delta = 0.195 mm).

The XIENCE V EECSS has received CE mark approval on 30 January 2006 and FDA approval 02 July 2008. In light of that, the SPIRIT V study has completed enrollment in approximately 100 sites outside the United States, and enrolled 3025 patients. It consists of two concurrent studies: a prospective, randomized, active-controlled, single blind, parallel two-arm multicenter study comparing XIENCE V to the Taxus Liberté™ in the treatment of diabetic patients with coronary artery lesions and a prospective, single arm, multi-center registry evaluating performance of XIENCE V in real-world use. In the registry, 30 day rates of in-hospital non-Q wave MI (1.9%), acute stent thrombosis (0.15%) and sub-acute stent thrombosis (0.3%) supported the acute safety of the XIENCE V EECSS. At 1 year the composite of Cardiac Death, MI attributed to the target vessel and TLR was 5.1% and the late definite and probable stent thrombosis was 0.23% with a cumulative rate of definite and probable stent thrombosis of 0.66% thus demonstrating the continued safety and efficacy of the XIENCE V EECSS.

In the Reality Studyxix, a large multi-centre study with a ‘real world’ patient population, the CYPHER™ arm MACE rate was reported at 240 days as 9.2% vs. 10.6% ( $p=ns$ ) in the TAXUS® arm, with an in-stent late loss of 0.09 mm vs. 0.31 mm ( $p<0.0001$ ) and an in-stent restenosis rate of 7.0% vs. 8.3% ( $p=ns$ ) respectively.

In another trial with similar randomization arms, but from a single centre; the Sirtax Trialxx, the reported MACE rates were 6.2% for the CYPHER™ arm at 270 days vs. 10.8% for the TAXUS® arm ( $p 0.009$ ) with in-stent late loss of 0.13 mm vs. 0.25 mm ( $p<0.001$ ) and in-stent restenosis rates of 3.2% vs. 7.5% respectively ( $p 0.013$ )xx.

A third study including only diabetic patients; the ISAR-Diabetes Trialxxi had a smaller sample size population (125 in each arm) and reported no differences in MACE rates at 9 months but an in-stent late loss of 0.19 mm in the CYPHER™ arm vs. 0.46 mm ( $p<0.001$ ) in the TAXUS® arm and restenosis rates of 6.9% vs. 16.5% respectively ( $p=0.03$ )xxi. This data is corroborated by IVUS dataxxii and suggest that CYPHER™ may perform better than TAXUS® in terms of late loss. However there has been no randomized control trial with a clinical primary endpoint that has shown superiority of one DES over the otherxxiii. As SPIRIT II has demonstrated that XIENCE V is superior to TAXUS in terms of late loss, this study will compare XIENCE V to CYPHER™.

In light of the recommendations from the Policy Conference on Cardiovascular Diseases in Women of the European Society of Cardiology, SPIRIT WOMEN is designed to focus on specific aspects of women’s health in relation to coronary artery disease, such as menopausal status, use of hormonal contraceptives or their surrogates, the referral path and symptoms at presentation, to better characterize the female population undergoing stent implantation and to continue the evaluation of safety and performance of XIENCE EECSS in real-world use in this specific population.

